## 7 ELIGIBILITY CRITERIA

### 7.1 Inclusion Criteria

Family carers of relatives with dementia need to be 18 years or over, providing care or support (or having done so in the past) to a relative with dementia and willing to provide informed consent to participate in the study

Alzheimer's Society Dementia Advisers and Managers need to be 18 years or over and willing to provide informed consent to participate in the study.

Dementia Advisers must be currently employed by the Alzheimer's Society actively fulfilling their role.

### 7.2 Exclusion Criteria

None

## 8 RECRUITMENT

Dementia Advisers in both phases will be identified and nominated by the Alzheimer's Society, as will managers and carers. Family carers of relatives with dementia from South Asian backgrounds will be identified and approached via the London Dementia Network, Camden and Islington NHS Foundation Trust Memory Services, and Bradford based community organisations with whom co-applicant [name] has collaborated with in previous studies.

The Alzheimer's Society will provide nominated staff and carers with Participant Information Sheets, and refer prospective participants to the research team. The research team will make contact no less than 24H later, provide further details regarding the study if needed and extend an invitation to participate in the study.

In the case of family carers of relatives with dementia from South Asian backgrounds, some prospective participants may have already agreed to be contacted for research (as trusts may have a register), but we will still approach a clinician beforehand to ensure there have been no changes and ask, if possible, if they can initiate contact. Clinicians or social workers will provide prospective participants with Participant Information Sheets (PIS) detailing the purpose of the study and what participation in the study entails, and obtain verbal consent and/or confirmation for referral to the research team. Participant Identification Centres will be asked to verbally provide potential

participants details. In cases where written information is provided in hard copy or electronically, these will be stored following procedures outlined above, and any emails permanently deleted immediately after. The research team will make contact no less than 24H later, provide further details regarding the study if needed and extend an invitation to participate in the study. Members of the research team will obtain informed consent from all participants that have agreed, following procedures described in section 6 of this document.

## 9 STATISTICAL METHODS

This is an implementation study not designed to assess clinical and cost effectiveness of START which is already established. Quantitative measures will be summarised simply using descriptive statistics. The study does not necessitate any other statistical considerations.

## 10 PATIENT AND PUBLIC INVOLVEMENT (PPI)

We will ensure public and patient involvement (PPI) throughout the research and implementation. We consulted the Alzheimer's Society Research network (ASRN) on the project development and methodology. [name] (co-applicant) will lead PPI. We will ensure we have south Asian carer representation and ask members of the ASRN to advise throughout, including on the steering and project management committee. We would review the AS's role in supporting wider-implementation of START with the research team in the final year of the grant.

## 11 FUNDING AND SUPPLY OF EQUIPMENT

The study funding has been reviewed by the UCL Research Office, and deemed sufficient to cover the requirements of the study. The research costs for the study have been supported by The Alzheimer's Society with a grant of £397,517.17 awarded in August 2017.

The project manager, will work for the three years organising the whole project, leading the ethics and local submission, recruiting and interviewing, beginning and co-ordinating the CFIR completion, being one of two coders of qualitative interviews, co-ordinating the new manuals completion, delivering the intervention to some of the English-speaking South Asian carers, writing up and line managing the research assistant (total cost £145,413.97). The RA will be employed for 2.25 years from February 2018 at grade 6B gathering and analysing data, and delivering some of the interventions phase. The manager and RA will each require a computer (cost £724.53 each). We estimate we will require 40 qualitative interviews and plan to give participants £30 vouchers as a token for their time at a cost of £1,200. We will need two digital recorders for the qualitative interviews (Total £147.82). For safety and so participants can reach them both researchers will have a mobile phone. Costs are £20/month plus VAT; a total this will be 60 months allowing for inflation over the three years (487.96) We will pay Way with Words for interviews transcription £1.20 + VAT per minute of individual audio-recording. We estimate that individual interviews will be an hour and focus groups take longer to transcribe - 40 would cost £4,554.66 in total. Translation costs are £40+VAT per hour of interpreter time or around £200 to translate roughly 1.5 pages of A4 text. Currently the leader and carer version are each 173 pages long but as there are many pictures and the text is spread out we estimate that this is equivalent to about 86 pages so translation should be £5,733, with back translation the same and then some smoothing out at around £2,000. We also estimate we will need 20 hours of interpreters for the qualitative interviews = £960 plus VAT. Total translation cost including VAT £17,624.05. We have costed for one session (half a day) of [name]'s time from January 2018 for her expertise in cross cultural work (prior to that from NIHR grant; total £24,115.71). We have also costed for one day a week of [name] time on the

project to take a lead part in producing the new manuals, and to train therapists in the intervention and supervise its delivery (total £63,562.92) We have also costed for 2 hours of [name]'s time from May 2019 to lead on qualitative interviews (prior to that from Wellcome fellowship. Total £5,366.78). We have costed [name]'s salary at 2 hours a week after the end of her Bradford fellowship (£4,127) to liaise between UCL and Bradford and interview in Bradford. We have costed for £6000 to pay for interviewing, training, intervention delivery by and supervision of three Dementia Advisers from the AS in discussion with the AS. This is at £12.94 per hour = 463 hour. This encompasses an estimated 50 hours of interviews and travel before and after the intervention about barriers, facilitators and how it worked, 120 hours of training/ travel to and from training, 30 hours to recruit the participants, 156 hours to deliver intervention an/travel to people's home, 10 hours of phone calls to make arrangements, 28 hours of write up about sessions, 70 hours of supervision/ travel. The cost of training the bilingual worker and them delivering the intervention will be similar. The cost of training the bilingual worker and them delivering the intervention will be similar.

We have costed for 12 return travel between Bradford and London at £138 return. [name] will visit London or our team will visit Bradford every three months, to interview people from South Asian community or to or liaise about the project. We have costed for 12 return trips at £150 for off peak fares for [name] to come to project meetings and advise and supervise on the evaluation We have also budgeted travel for the researchers to interview and deliver the intervention, assuming an average of £10 per return visit (total £6000) We expect to have three steering group meetings and eight project group meetings over the life of the project and have budgeted £3,817.28 for meeting costs, including lunch and local travel (as it is cheaper for travel to be off peak). We have budgeted for 2 PPI members to attend the steering and management meetings at £50 per meeting (£1,200). We have budgeted £150 for stationery as we have to write to participants to confirm interviews and provide manuals.

## 12 DATA HANDLING AND MANAGEMENT

This project has been registered with the UCL Data Protection Team (registration number: Z6364106/2018/01/57). All information gathered will be kept strictly confidential and held in accordance with the principles of the Data Protection Act (1998), and according to UCL information governance procedures. Alzheimer's Society staff will work in accordance with the Alzheimer's Society data handling and management procedures.

Hard copy data of participant consent forms will be stored at the Division of Psychiatry, UCL, in a secure locked location accessible only by researchers.

Each participant will be assigned a unique identifying number the key of which will be kept electronically in the study's UCL shared drive accessible only by the UCL research team. All data will be stored without subject name or contact details. Data will be held on a secure database on a password-protected computer at University College London. Access to data will be restricted to appropriate members of the research team. In order to enable follow-up contacts, it will be necessary to identify the participants, but access to contact details (e.g. name and address) will be restricted to key members of the research team.

Participants will be informed how data will be managed as part of the consent procedure. Rules governing the conduct of the focus groups will be discussed at the beginning of each group and participants will be requested not to discuss others' contributions outside the group.

Audio recordings from focus groups/interviews and training sessions will be uploaded to the UCL Data Safe Haven as soon as possible after they are acquired. Once uploaded recordings will be

deleted from recording devices. Audio files will be sent to a professional UK-based commercial transcription service (WAY with Words) that has strong data protection, confidential storage and removal from the transcription service database when complete. After data processing the data will be archived and stored securely in accordance with UCL protocols.

Co-applicants [name] and [name] will act as custodians of data at the University of Bradford and the University of Exeter respectively, who are required by law to comply with the data protection Act, 1998. No identifiable data will be transferred between study sites (i.e. London, Bradford and Exeter Universities) over the course of the study. In order to ensure security of anonymised data during transfer of data between study sites, data will be transferred via University Email accounts only, downloaded and stored following procedures outlined above, and permanently deleted from electronic inboxes immediately after.

Participant Identification Centres will be asked to verbally provide potential participants details. In cases where written information is provided in hard copy or electronically, these will be stored following procedures outlined above, and any emails permanently deleted immediately after.

### **13 MATERIAL/SAMPLE STORAGE**

Not applicable

### **14 PEER AND REGULATORY REVIEW**

The study has been peer reviewed in accordance with the requirements outlined by UCL.

Choose either (having discussed with the UCL/UCLH Research Office):

- The Sponsor considers the procedure for obtaining funding from the Alzheimer's Society to be of sufficient rigour and independence to be considered an adequate peer review.

The study was deemed to require regulatory approval from the following bodies: Health Research Authority Research Ethics Committee. Approval will be obtained before the study commences.

### **15 ASSESMENT AND MANAGEMENT OF RISK**

In delivering the intervention to family carers of relatives with dementia, Dementia Advisers will work according to the Alzheimer's Society's Risk Management policies. An important aspect of supervision of the researchers delivering the intervention to family carers from South Asian backgrounds will be to identify and respond to any risks identified during the course of assessment or intervention. Researchers will be provided with specific training in how to respond to any risks disclosed by carers, in relation to harm to both themselves and the person they were caring for. Researchers will be asked to speak to the lead investigator if the abuse Modified Conflict Tactic Score (MCTS) (34, 35) is in the possibly abusive range ( $\geq 2$ ) or if they had any concerns about potential abuse. Similarly, if carers reported high levels of depression or anxiety, this will be discussed with the lead investigator. If concerns are raised, a plan will be made with the lead investigator about how to manage the risk and information will be shared with the local clinical teams. Time will also be taken within supervision to highlight the importance of behaving ethically and safely in all aspects of clinical work, for example reflecting on maintaining clear boundaries

clinically and how to practise safely when working alone in people's homes. Researchers will work to UCL's Lone Working standard in cases where they visit the family carer at their home.

## 16 RECORDING AND REPORTING OF EVENTS AND INCIDENTS

### 16.1 Definitions of Adverse Events

| Term                                                                                                                                                                                                                                                                                                                                                                                                                                      | Definition                                                                                                                                                                                                                                                                                                                                                 |
|-------------------------------------------------------------------------------------------------------------------------------------------------------------------------------------------------------------------------------------------------------------------------------------------------------------------------------------------------------------------------------------------------------------------------------------------|------------------------------------------------------------------------------------------------------------------------------------------------------------------------------------------------------------------------------------------------------------------------------------------------------------------------------------------------------------|
| Adverse Event (AE)                                                                                                                                                                                                                                                                                                                                                                                                                        | Any untoward medical occurrence in a patient or study participant, which does not necessarily have a causal relationship with the procedure involved.                                                                                                                                                                                                      |
| Serious Adverse Event (SAE).                                                                                                                                                                                                                                                                                                                                                                                                              | Any adverse event that: 
 
• results in death,
 
• is life-threatening*,
 
• requires hospitalisation or prolongation of existing hospitalisation**,
 
• results in persistent or significant disability or incapacity, or
 
• consists of a congenital anomaly or birth defect
 
 |
| 
*A life- threatening event, this refers to an event in which the participant was at risk of death at the time of the event; it does not refer to an event which hypothetically might have caused death if it were more severe.
 
** Hospitalisation is defined as an in-patient admission, regardless of length of stay. Hospitalisation for pre-existing conditions, including elective procedures do not constitute an SAE.
 |                                                                                                                                                                                                                                                                                                                                                            |

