## 2 BACKGROUND AND RATIONALE

Family carers of people with dementia experience higher levels of psychological burden than carers of other people with chronic illness (1, 2), with up to 40% showing clinical levels of depression and anxiety (3, 4). Maintaining the health of family carers of people with dementia is socially and economically important (5, 6) as it may prevent or delay care home entry by improving family carers wellbeing so they can continue caring (5).

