### 16.2.3 Expectedness

| Category        | Definition                                                                                                                                                                                                     |
|-----------------|----------------------------------------------------------------------------------------------------------------------------------------------------------------------------------------------------------------|
| Expected | An adverse event which is consistent with the information about the procedure listed in the Investigator Brochure, SPC, manual of Operation (amend as appropriate) or clearly defined in this protocol. |

|                   |                                                                                                                                                                                                    |
|-------------------|----------------------------------------------------------------------------------------------------------------------------------------------------------------------------------------------------|
| Unexpected | An adverse event which is not consistent with the information about the procedure listed in the manual of operation (or other – amend as appropriate)* or clearly defined in this protocol. |
|-------------------|----------------------------------------------------------------------------------------------------------------------------------------------------------------------------------------------------|

\* this includes listed events that are more frequently reported or more severe than previously reported

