### 16.4 Procedures for recording and reporting Serious Adverse Events

All serious adverse events will be recorded in the medical records and the CRF, and the sponsor's AE log.

All SAEs (except those specified in section 16.5 as not requiring reporting to the Sponsor) must be recorded on a serious adverse event (SAE) form. The CI/PI or designated individual will complete an SAE form and the form will be preferably emailed to the Sponsor within 5 working days of becoming aware of the event. The Chief or Principal Investigator will respond to any SAE queries raised by the sponsor as soon as possible.

Where the event is unexpected and thought to be related to the procedure this must be reported by the Investigator to the Health Research Authority within 15 days.

Completed forms for unexpected SAES must be sent within 5 working days of becoming aware of the event to the Sponsor

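### The hospitalisation footnote to the SAE definition makes no exception for unplanned admission due to worsening of a pre-existing condition, so a carer's admission for worsened depression or anxiety is not serious on that criterion

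*Protocol*

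**What the plan says.** Protocol section 16.1 makes an adverse event serious if, among other criteria, it "requires hospitalisation or prolongation of existing hospitalisation". A double-asterisk footnote on that criterion does two things. It first defines the term broadly: "Hospitalisation is defined as an in-patient admission, regardless of length of stay". It then takes a class of admissions out: "Hospitalisation for pre-existing conditions, including elective procedures do not constitute an SAE". Three other criteria are relevant to adult carers and do not carry that footnote: death, an event that "is life-threatening", and one that "results in persistent or significant disability or incapacity".

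Section 16.2 requires every adverse event to be assessed for severity, causality, seriousness and expectedness. Section 16.3 sends adverse events to the sponsor as soon as they are known. Section 16.4, which is headed as the SAE procedure, adds an SAE form within 5 working days and an external report: "Where the event is unexpected and thought to be related to the procedure this must be reported by the Investigator". That report goes to the Health Research Authority, with a limit of 15 days.

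On the population, section 2 describes carers of people with dementia as a group "with up to 40% showing clinical levels of depression and anxiety", and says the intervention was developed to help carers with those symptoms. Section 7.2 lists no exclusion criteria.

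**The concern.** An exclusion for pre-existing conditions is normally meant to keep planned care, such as a long-booked operation, out of the SAE count. This footnote goes further. It turns on whether the condition existed beforehand, not on whether the admission was planned or the condition had worsened.

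That matters more here than in most studies, because a common pre-existing condition among these carers is also what the intervention addresses. Worsening mood is the natural harm to look for in a psychological intervention aimed at mood. That is an inference; the protocol does not say it. A site applying the footnote literally to a carer with depression at entry, who deteriorates during the sessions and is admitted, would record the event as non-serious. At stake is how such an event is classified and whether it reaches the SAE form and the 15-day external report, even if it is judged related and unexpected.

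**Working it through.** No sample size, power or error rate is involved, and the protocol gives no figure to reproduce. The check is a reading of the rules in order, applied to one case: a carer with depression at entry, admitted unplanned because it has worsened, with no immediate risk of death and no lasting disability.

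1. **Can such a carer be enrolled?** Yes. Section 7.1 asks that carers be adults, have given care or support to a relative with dementia, and be willing to consent. Section 7.2 excludes no one.
2. **Is it an adverse event?** Yes. The definition in 16.1 covers untoward medical occurrences whatever their cause and has no carve-out for worsening.
3. **Is it serious by hospitalisation?** It is an in-patient admission, so the criterion is met at first. The footnote then removes it, because the condition pre-dates the study. The word introducing elective procedures marks them as one example of what is removed, not as its limit. No other section makes an exception for unplanned admission or deterioration.
4. **Is it serious by another criterion?** Not in this case. It would be if the event were fatal, life-threatening or disabling.
5. **What still happens?** Assessment for severity, causality, seriousness and expectedness (16.2) and immediate notice to the sponsor (16.3).
6. **What does not happen?** The SAE form in 16.4 is not required. The 15-day rule speaks of the event without repeating that it must be serious, but it stands in the SAE section. On its natural reading it is not reached either.

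**Carers exposed to the gap**

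- Phase 2 carers, from the participant groups part of section 4: up to 9 third-sector + up to 13 South Asian = up to 22.
- At the section 2 figure of 40%: 0.40 × 22 = 8.8, about 9.
- At an assumed 20%, for range: 0.20 × 22 = 4.4, about 4.

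These count carers who might start with clinical-level symptoms, not admissions. The protocol gives no admission rate, so the number of misclassified events cannot be calculated. Carers with another chronic illness fall under the same footnote for that illness.

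**The case against.** The strongest case against is that little is lost. The sponsor hears of every adverse event immediately under 16.3, which is sooner than the 5 working days for the SAE form. Causality and expectedness are still judged under 16.2. Section 15 adds a route by which high depression or anxiety is discussed with the lead investigator and, if there are concerns, a plan is made and local clinical teams are informed. Section 9 plans only descriptive summaries, and no stated analysis or decision depends on an SAE count.

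Most of this stands and limits the seriousness of the point. It does not remove it. Notice to the sponsor under 16.3 does not itself require the SAE form or the external report. The section 15 route concerns managing risk, not classifying events, and is written for the researchers; Dementia Advisers follow the Alzheimer's Society's own policies.

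A reader might also infer more than the protocol supports:

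- **That such an admission can never be an SAE.** The exclusion attaches only to hospitalisation; the death, life-threatening and disability criteria still apply.
- **That the study population is defined by depression or anxiety.** Entry depends on being a carer. The 40% is an upper figure from cited literature on carers in general.
- **That the footnote contradicts the one in 16.2.3, which for unexpected events says "this includes listed events that are more frequently reported or more severe than previously reported".** That note concerns expectedness and compares with earlier reports of listed events, not with a participant's own baseline. Seriousness and expectedness are separate judgements, and an event can be non-serious and unexpected without contradiction.
- **That about 9 events would be missed.** The figure is an upper bound on carers exposed.

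**Conclusion.** The point holds in a limited form. As written, the footnote classes an unplanned admission for a worsened pre-existing condition, depression and anxiety included, as non-serious unless the event is fatal, life-threatening or disabling. The consequence is a missing SAE form and, on the natural reading of 16.4, a missing 15-day report for an event judged unexpected and related. The event is not hidden from the sponsor.

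Up to about 9 of 22 carers could be exposed, or about 4 at an assumed 20%. This takes full Phase 2 recruitment and supposes that the cited prevalence carries over to this sample. Few admissions are likely in a group this small, so this is a clear but modest defect of wording that should be corrected, and it does not threaten the study. Left as it is, a later statement that no related SAEs occurred could partly reflect the definition.

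**What to change.** Amend the footnote in 16.1 so that it excludes only planned or elective admissions for a pre-existing condition that has not worsened since consent. Add that an unplanned admission for deterioration of a pre-existing condition, including depression or anxiety, remains an SAE and is handled under 16.2 and 16.4. In the same amendment, state in 16.4 whether the 15-day report applies to SAEs only. No change to 16.2.3 is needed.

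The cost is a sentence or two by protocol amendment and at most a few more SAE forms among up to 22 carers. Data collection and analysis are unaffected.
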